## 4.2 Clinical investigation site

The clinical investigation will be performed at the Reha Zentrum Münster Betriebs GmbH, [name], Austria.

## 4.3 Responsible ethics committee

The responsible ethics committee (EC) for this clinical investigation is the Ethics Committee of the Medical University of Innsbruck.

## 4.4 Study registration

Once a favourable opinion has been obtained from the ethics committee, an application will be submitted for inclusion in the German Clinical Trials Register (DRKS) or another primary register in accordance with WHO criteria

## 4.5 Data collection

After eligibility screening, a screening for cognitive impairment (Scr) will be performed. In eligible patients who pass the cognitive screening, study specific assessment data will be collected at baseline (T1) and post-intervention (T2) at 4 weeks after completion. Assessments will be performed at similar daytimes to increase comparability. Information on demographic and disease specific patient characteristics will be extracted from patients' charts. Further disease-specific data will be collected by neurologists (PI, investigator), cognitive screening will be performed by psychologists as part of the clinical routine, and movement and function-related data will be collected by trained physiotherapists. The study participants will be

supported as required and as permissible with respect to the test instructions, and they may take a rest at any time.

## 4.6 Screening data

Screening for cognitive and walking impairment will be performed using two assessment strategies for each as presented in Table 5. The Mini Mental State Examination and a neurological exam are **performed within clinical routine** at the Reha Zentrum Münster (**highlighted green**), the Functional Ambulation Categories are performed **by the study PI or investigator as part of the clinical investigation (highlighted yellow) and does not involve any activity of the patient**.

**Table 5:** Screening

| Parameters         | Assessment                             | Patient inclusion if         | Scr |
|--------------------|----------------------------------------|------------------------------|-----|
| Cognitive function | Mini Mental State Examination (MMSE)   | ≥24/30 points                | x   |
| Walking impairment | Neurological exam                      | Walking impairment confirmed | x   |
| Walking impairment | Functional Ambulation Categories (FAC) | 0-4 points                   | x   |

Abbreviation: Scr=Screening.

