|                      | 
investigation. If they express their interest in participating, they will be screened by a psychologist for cognitive impairment and for walking impairment using the Functional Ambulation Categories in addition to a neurological exam. If patients pass the screening (if Mini Mental State Examination <math>\geq 24/30</math> points, walking impairment, FAC 0-4/5 points)), written informed consent will be obtained from them, followed by a Baseline examination. Then, the clinical investigation intervention will be conducted for 4 weeks, and a semi-structured observation of the intervention at weeks 1 and 4. After the post-intervention examination, the clinical investigation will be terminated.
                                                                                                                                                                                                                                                                                                                                                                                                                                                                                                                                                                                                                                                                                                                                                                                                                                                                                                                                                                                                               |

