**Secondary endpoints**

The secondary endpoints for this clinical investigation and how they will be assessed are presented in Table 7. The validated German version of all assessments will be used, which have demonstrated good to excellent properties. In addition, the collection timepoints are shown. The assessments which will be ***performed in clinical routine are highlighted in green***, with the remaining assessments being ***performed as part of the clinical investigation (highlighted yellow)***.

**Table 7:** Secondary endpoints and assessment

| No. | Secondary endpoint | Assessment                                                   | Scr | BL  | PI | IV |
|-----|--------------------|--------------------------------------------------------------|-----|-----|----|----|
| 1.1 | Number of falls    | Falls log [ambulatory patients] (see CRF)                    |     | x   | x  |    |
| 1.2 | Walking ability    | Functional Ambulation Categories (FAC) [ambulatory patients] | x   | (c) | x  |    |

|      |                                                                                                           |                                                                                       |    |   |    |   |
|------|-----------------------------------------------------------------------------------------------------------|---------------------------------------------------------------------------------------|----|---|----|---|
| 1.3  | Walking speed                                                                                             | 10-Metre Walk Test (10MWT)
[ambulatory patients, assessed in clinical routine]     |    | x | x  |   |
| 1.4  | Dynamic balance during walking                                                                            | Functional Gait Assessment (FGA)
[ambulatory patients]                             |    | x | x  |   |
| 1.5  | Walking distance                                                                                          | 6-Minute Walk Test (6MWT)
[ambulatory patients, assessed in clinical routine]      |    | x | x  |   |
| 1.6  | Functional mobility                                                                                       | Timed Up and Go test (TUG)
[ambulatory patients]                                   |    | x | x  |   |

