| 1.7  | Dynamic balance                                                                                           | Four-Square Step Test (FSST)
[ambulatory patients]                                 |    | x | x  |   |
| 1.8  | Trunk movement                                                                                            | Trunk Control Test (TCT) [non-ambulatory patients]                                    |    | x | x  |   |
| 1.9  | Limits of stability with respect to trunk movements                                                       | Modified Functional Reach Test (MFRT) [non-ambulatory patients]                       |    | x | x  |   |
| 1.10 | Fall-related self-efficacy                                                                                | Falls Efficacy Scale- International Version (FES-I)                                   |    | x | x  |   |
| 1.11 | Health-related quality of life                                                                            | 5-level EQ-5D version (EQ-5D-5L)                                                      |    | x | x  |   |
| 1.12 | Depression                                                                                                | Beck Depression Inventory, second edition (BDI-II)                                    |    | x | x  |   |
| 1.13 | Fatigue                                                                                                   | Fatigue Severity Scale (FSS)                                                          |    |   | x  |   |
| 1.14 | Goal definition and evaluation of its achievement                                                         | SMART defined movement-related individual goal (a); Goal Attainment Scaling (GAS) (b) | ax |   | bx |   |
| 1.15 | Gait parameters (gait speed, walking distance, number of steps and step length)                           | Measured by LEXO® during the intervention as part of the clinical routine             |    |   |    | x |
| 1.16 | Body weight and gait support (percentage of body weight support, percentage of active/passive gait modes) | Measured by LEXO® during the intervention as part of the clinical routine             |    |   |    | x |

Abbreviation: Scr=screening; SMART=specific, measurable, attractive, realistic and terminated; c=data carryover to baseline if patient has passed the screening; BL=baseline; PI=post-intervention; IV=intervention period (at all intervention sessions)

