## Standardised assessment description

All chosen standardised assessments are valid, reliable and responsive to change. Validated German versions will be used as can be seen from the CRF.

The Functional Ambulation Categories (FAC) (Mehrholz et al., 2007; Wade, 1992) will be used in its validated German version (Klotz et al., 2019) to screen patients with respect to their walking ability and to assess walking ability post-intervention. The FAC is a 6-point functional walking test that evaluates ambulation ability, determining how much human support the patient requires when walking, regardless of whether or not they use a personal assistive device. The FAC is a quick visual measurement of walking, is simple to use, easy to interpret, and cost-effective because only stairs and 15m of indoor floor are needed to administer the test

The 10-Metre Walk Test (10MWT) (Bohannon, 1997) is a performance measure used to assess walking speed in meters per second over a short distance. It can be employed to determine functional mobility in various neurological populations. The 10MWT was originally developed to measure walking capacity in patients with stroke (Wade et al., 1987) and was shown to be valid and reliable in a mixed group of neurological patients (Rossier & Wade, 2001). Its psychometric properties have been well investigated in adult patients with incomplete spinal cord injury showing good reliability and excellent responsiveness (van Hedel et al., 2006; van Hedel et al., 2005). In these patients, walking speed could also predict functional walking performance well (van Hedel, 2009). In adult patients with stroke, the 10MWT proved sensitive to change (Salbach et al., 2001). The required equipment includes a stopwatch and a clear pathway with set a distance of 10 metres. The set-up involves marking the 10-metre walkway and adding a mark at 2 and 8 metres. Instructions are as follows: The patient walks without assistance for 10 metres, with the time measured for the intermediate 6 meters to allow for acceleration and deceleration. Assistive devices may be used but must be kept consistent and documented for each test. Timing is started when the toes pass the 2-metre mark and timing is stopped when the toes pass the 8-metre mark. The 10MWT can be tested at either preferred walking speed or maximum walking speed. In this clinical investigation the test will be performed at maximum speed. Two trials will be performed and the average calculated (Watson, 2002).

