## 7. STUDY PROCEDURES

### 7.1. Assessment and treatment schedule

The clinical investigation will comprise a screening, a baseline examination (T1), 16 intervention units over 4 weeks, and a post-intervention examination (T2).

The duration and number of the examinations (Table 1) will be used in addition to the patient's regular inpatient rehabilitation treatment. The intervention itself and some assessments will be performed as part of the clinical routine (for details, see Chapter 4). The PI, investigator and psychologists will perform any disease and cognition related examinations. All therapists conducting the movement-related assessments will be trained, and they will therefore work based on the same principles. Furthermore, the physiotherapists at the study site are using some the assessments on a daily basis (e.g., 10MWT, 6MWT), but for ensuring consistency, their training will be refreshed. The clinical investigation team (physiotherapists) that will conduct the RAGT intervention are trained on the use of the LEXO® device by authorised personnel from Tyromotion. In addition, the LEXO® is used also in the clinical routine at the Reha Zentrum Münster, which is why the physiotherapy team is familiar with the procedures. The clinical investigation team (physiotherapists) that will perform the motor assessments in this study will undergo training from [name] who is an experienced neurological physiotherapist and senior researcher to ensure consistency. In Table 8, the study procedures and schedule are presented; the table includes both the procedures which are performed ***within the clinical routine (highlighted green)*** and ***in addition to the clinical routine (highlighted yellow)***.

**Table 8:** Treatment and assessment regimen of a (screened, potential\*) study participant

| Procedure                                       | Dosage | Time                                                                            | Duration within clinical routine | Duration in addition to clinical routine |
|-------------------------------------------------|--------|---------------------------------------------------------------------------------|----------------------------------|------------------------------------------|
| Screening*                                      | 1x     | After checking for eligibility by the PI/investigator and the patient's consent | 10-15 min                        | --                                       |

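### The protocol does not ensure the same rater and method for the two FAC values compared in secondary objective 2, and the baseline value is also the entry rating

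*Protocol*

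**What the plan says.** **Baseline value.** Section 4.6 has the screening FAC done "by the study PI or investigator as part of the clinical investigation (highlighted yellow) and does not involve any activity of the patient". Table 7 (Section 4.8) marks the FAC at screening and post-intervention. In the baseline column it has only a bracketed letter, explained in the footnote as "c=data carryover to baseline if patient has passed the screening". No new FAC is taken at T1.

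**Method.** The assessment description in Section 4.8 gives a single account of the FAC, covering both screening and post-intervention use. It calls the FAC a functional walking test and a quick visual measure of walking, for which "only stairs and 15m of indoor floor are needed to administer the test".

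**Raters.** Section 4.5 states that "movement and function-related data will be collected by trained physiotherapists". Section 7.1 states: "The PI, investigator and psychologists will perform any disease and cognition related examinations". Sections 6.4 and 7.1 provide training in the motor assessments for the physiotherapists who perform them, for the sake of consistency. The synopsis (Study procedures) says of interested patients that "they will be screened by a psychologist for cognitive impairment and for walking impairment using the Functional Ambulation Categories in addition to a neurological exam".

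**Use.** FAC change is secondary objective 2 (Section 2.3), and functional ambulation is in the null hypothesis (Section 2.4). Section 8.2 lists the FAC as ordinal and tests ordinal data pre-post by Wilcoxon signed rank on the total sample at two-sided 0.05. The limitations list records that there is no control group. Entry requires FAC 0-4 and a walking impairment confirmed by neurological exam (Table 5).

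**The concern.** A pre-post change in an ordinal rating is interpretable only if both ratings are made in the same way. Here one end is a rating by a neurologist during screening, described as needing nothing from the patient. The other end falls, by the general division of labour, to physiotherapists using a walking test. If that is what happens, a shift in FAC could come from the change of rater or procedure with no change in the patient, and no comparator arm would absorb it.

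A second problem does not depend on who rates at T2. The same single rating both admits the patient and serves as the starting point of the change score, so any error in it enters both.

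At stake is the interpretation of one secondary endpoint, in a study that wants to examine how far the training caused the outcomes (Section 4.1) and to inform a later randomised trial.

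**Working it through.** **1. The two values side by side**

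| | Baseline FAC | Post-intervention FAC |
|---|---|---|
| Source | Screening value carried over (Table 7) | New rating (Table 7) |
| Rater | PI or investigator (4.6) | Not named; physiotherapist by inference from 4.5 and 7.1 |
| Method | No patient activity (4.6), but a walking test in 4.8 | Walking test (4.8) |

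The left column contradicts itself on method, since a walking test without patient activity is not possible as worded. The right column leaves the rater open. If the PI or investigator also rates T2, that sits badly with Sections 4.5 and 7.1. If T2 is also rated without activity, that contradicts Section 4.8. Every reading leaves a conflict, and none fixes one rater group and one method.

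**2. The entry rule**

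- True FAC 5 rated 4: can be enrolled, and a correct T2 rating of 5 counts as a gain of one.
- True FAC 4 rated 5: excluded, so no offsetting loss is ever recorded.
- True FAC 3 rated 4: enrolled, and a correct T2 rating counts as a loss of one.
- True FAC 4 rated 3: enrolled, and counts as a gain of one.

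Only errors across the 4/5 boundary are one-directional.

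**3. What a systematic difference would do to the planned test**

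The sample size reproduces from the strata in Section 5.3: 4 × 5 + 4 × 2 = 28. The protocol gives no figure for FAC rating disagreement, so everything below is assumed: no true change, and differences of one category only. All non-zero differences then have equal rank, and the Wilcoxon test reduces to a sign test on the non-tied pairs:

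- asymptotic: |z| = |up − down| / √(up + down)
- exact, with k differences all one way: p = 2 × 0.5^k

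Results:

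- k = 4: z = 4/√4 = 2, asymptotic p = 0.0455; exact p = 2 × 0.5^4 = 0.125. 4/28 = 14%.
- k = 6: exact p = 2 × 0.5^6 = 0.031. 6/28 = 21%.

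False-positive rates from 200,000 simulated trials per scenario, asymptotic / exact:

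| Rated up / down | n = 28 | n = 25 | n = 23 |
|---|---|---|---|
| 10% / 10% | 4.9% / 1.1% | 4.9% / 0.9% | 4.8% / 0.8% |
| 15% / 5% | 20.4% / 8.5% | 18.8% / 6.3% | 17.4% / 5.0% |
| 20% / 5% | 34.6% / 20.8% | 31.4% / 16.4% | 29.3% / 13.5% |
| 20% / 0% | 83.9% / 50.0% | 76.7% / 38.3% | 70.4% / 30.6% |

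Here n = 25 reflects the expected 10% attrition (28 × 0.9 = 25.2). n = 23 leaves out the five severe subacute stroke patients (28 − 5), because Table 7 labels the FAC for ambulatory patients although secondary objective 2 has no such limit. Balanced disagreement does not inflate the error; a systematic difference does.

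**The case against.** The strongest reply is that the protocol never prescribes two methods. Section 4.8 gives one FAC description for both uses, Section 4.6 gives the FAC to the PI or investigator, and nothing says that they do not rate it at T2 as well. A reader might infer that the plan compares a physician's no-activity rating with a physiotherapist's walking test. The documents do not establish that: the physiotherapist comes from a general sentence on movement data, not from a statement about the FAC. This part of the reply stands, and it limits the point to what the protocol fails to ensure.

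The no-activity phrase also has a harmless reading. It sits where routine and added procedures are separated, and the protocol uses similar language elsewhere about patient burden, for instance for the session observation. The rater may simply score walking seen at the routine neurological exam. That is possible, but the text does not say so, and the wording still clashes with Section 4.8.

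Three further readings go too far:

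- That a psychologist rates the FAC. The synopsis sentence is loosely built, and Sections 4.5, 4.6 and 7.1 separate the roles.
- That the PI or investigator is untrained in the FAC. Sections 6.4 and 7.1 are silent on that.
- That baseline errors inflate the change across the scale. This holds only at the 4/5 cut-off, and the required neurological confirmation of walking impairment should make such entries fewer.

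It is also fair that T1 falls on day 0-1 after inclusion, so the carry-over avoids repeating a recent rating, and that without a control group a FAC change could not be attributed to the training anyway. Neither removes the need for two comparable ratings.

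**Conclusion.** The point holds as a failure to secure a common rater and method for the two FAC values, together with a baseline that is also the entry rating. The carry-over, the no-activity wording and the walking-test description are explicit. The T2 rater is an inference.

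Whether bias results depends on a systematic difference between the two ratings, whose size and direction the documents do not give. A reader might take p = 0.031 as an expected result; it is not. It needs six one-category differences all in one direction, an assumed rate and pattern that no section supports, and the 4/5 mechanism alone would supply it only if all six were true FAC 5 patients rated 4. It shows only how few discordant ratings the test needs at this sample size.

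The consequence is confined to the FAC, one of 16 secondary endpoints in Table 7. The primary feasibility endpoint is untouched. The change is worth making because it is cheap.

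**What to change.** - Use the screening FAC for eligibility only.
- In Table 7, replace the carry-over mark in the baseline column with a cross, and delete the carry-over footnote.
- Have the FAC scored at T1 and T2 by the same rater group, the trained assessment physiotherapists, with the procedure in Section 4.8. Analyse the change from T1 to T2.
- Reconcile the synopsis (Study procedures), Sections 4.5 and 4.6, the Table 7 footnote and the FAC description in Section 4.8, so that each names the same rater and procedure. In the synopsis, limit the psychologist to the cognitive screening.

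A separate T1 rating also deals with the cut-off effect: a true FAC 5 patient admitted in error would be scored afresh at T1, and the screening error would no longer enter the change.

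The cost is wording plus a few minutes at T1. In ambulatory patients, the 10MWT and the FGA (which includes stairs) already show much of the walking needed to score the FAC.

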## 4.7 Demographic and disease-specific data

Standardised assessments for rating walking and overall motor ability, spasticity, overall impairment or disability in the different patient groups will either be **collected in routine care (highlighted green)** or **as part of the clinical investigation (highlighted yellow)** (see Table 6 for details). Disease specific instruments will be used as appropriate.

**Table 6:** Demographic and disease specific information checked at eligibility screening and collected at baseline

| Parameters                    | Assessment (if applicable) | BL |
|-------------------------------|----------------------------|----|
| Age (years; date of birth)    | --                         | x  |
| Gender: male, female, diverse | --                         | x  |
| Education (years)             | --                         | x  |
| Diagnosed disease             | As per defined criteria*   | x  |
| Date of initial diagnosis     | --                         | x  |
| Most affected body part       | --                         | x  |

|                                                                                          |                                                                                                                                                                                                                                         |   |
|------------------------------------------------------------------------------------------|-----------------------------------------------------------------------------------------------------------------------------------------------------------------------------------------------------------------------------------------|---|
| Impairment caused by a stroke                                                            | National Institutes of Health Stroke Scale, or NIH Stroke Scale (NIHSS) (Brott et al., 1989; Lyden et al., 1999), validated German version (Berger et al., 1999)                                                                        | x |
| Disability caused by MS                                                                  | Expanded Disability Status Scale (EDSS) (Kurtzke, 1983)                                                                                                                                                                                 | x |
| Disability and impairment in PD                                                          | Unified Parkinson's Disease Rating Scale (UPDRS) (Fahn & Elton, 1987)                                                                                                                                                                   | x |
| Functional disability caused by PD                                                       | Hoehn & Yahr Scale (H&Y) (Hoehn & Yahr, 1967)                                                                                                                                                                                           | x |
| Neurological level of injury in SCI                                                      | As per defined criteria*                                                                                                                                                                                                                | x |
| Classification of the acquired impairment in SCI                                         | American Spinal Injury Association (ASIA) Impairment Scale (AIS) (Kirshblum et al., 2011; Roberts et al., 2017) in its German version ("Traumatische Querschnittlähmung," 2019)                                                         | x |
| Impairment caused by ataxia due to MS, hereditary ataxia, GBS or stroke                  | Scale for the Assessment and Rating of Ataxia (SARA) (Schmitz-Hübsch et al., 2006; Weyer et al., 2007).                                                                                                                                 | x |
| Spasticity caused by a stroke, MS, spastic para- and tetraplegia or motor neuron disease | Modified Ashworth Scale (MAS) (Bohannon & Smith, 1987; Harb & Kishner, 2021)                                                                                                                                                            | x |
| Disability caused by GBS                                                                 | Guillain-Barré syndrome disability scale (GBSDS) (van Koningsveld et al., 2007) in its validated German version (aus: ( Diagnose und Therapie des Guillain-Barré Syndroms im Kindes- und Jugendalter , 4. Auflage, Version 1.0)) | x |
| Peripheral neuropathy e.g., due to GBS or CIDP                                           | Overall Neuropathy Limitations Scale (ONLS) (Graham & Hughes, 2006)                                                                                                                                                                     | x |
| Functional status and functional change in patients with ALS                             | Amyotrophic Lateral Sclerosis Functional Rating Scale, revised version (ALS-FRS-R) (Cedarbaum et al., 1999), in its validated German version (Abdulla et al., 2013)                                                                     | x |

Abbreviation: BL=baseline.

\*All diagnoses are made based on a clinical exam of the patient and supportive investigation:  
 (1) Stroke is diagnosed based on current criteria according to the Guideline of the German Society of Neurology (2017) (Hennerici & Kern, 2017)

- (2) MS is diagnosed according to the revised McDonald criteria valid at the time of diagnosis (Polman et al., 2011; Thompson et al., 2018).
- (3) (Idiopathic) PD is diagnosed according to the UK Brain Bank criteria (Hughes et al., 1992).
- (4) SCI is diagnosed based on current criteria according to the Guideline of the German Society of Neurology (DGN 2012) or current NICE Guideline (*Spinal injury: assessment and initial management. Spinal injury assessment: assessment and imaging for spinal injury. NICE Guideline NG41*, 2016) valid at the time of diagnosis.
- (5) Hereditary ataxia is diagnosed according to the Ataxia Medical Guidelines 2016 or earlier versions, developed by Ataxia UK, London (de Silva et al., 2019).
- (6) For GBS, the current diagnostic criteria are used (Willison et al., 2016). Chronic inflammatory demyelinating polyneuropathy (CIDP) is diagnosed according to diagnostic criteria of the European Federation of Neurological Societies/Peripheral Nerve Society Guideline on the management of chronic inflammatory demyelinating polyradiculoneuropathy- First Revision ("European Federation of Neurological Societies/Peripheral Nerve Society Guideline on management of chronic inflammatory demyelinating polyradiculoneuropathy: report of a joint task force of the European Federation of Neurological Societies and the Peripheral Nerve Society--First Revision," 2010) or earlier versions.
- (7) Motoneuron disease is diagnosed using the diagnostic criteria for ALS from the World Federation of Neurology as the El Escorial Criteria (Brooks, 1994), in their revised version as the Airlie House criteria (or El Escorial revised) (Brooks et al., 2000) and the Awaji criteria (de Carvalho et al., 2008). There are no formal criteria for progressive muscular atrophy (PMA) and primary lateral sclerosis (PLS). Recently, the Gold Coast criteria were developed and are proposed (Johnsen, 2020).

